**Fig. 2 Fig2:**
[figure not shown]
Cognitive Bias Modification (CBM) program screenshots

Phone Coach Adherence Promotion (AP) (Arm 3 Only). AP procedures are intended to mimic the effects of the nonspecific, yet likely important, support and instruction provided by research staff when CBM has been traditionally delivered in laboratories. This includes technical assistance with use of the program, support/encouragement, motivational enhancement, and brainstorming solutions to barriers to regular sessions. We hypothesize that the addition of AP will lead to greater participant adherence to the program and therefore better clinical outcomes. In the first 4 weeks of each youth’s enrollment, phone coaches will make between one and four brief, 10–30 min AP telephone calls to youth enrolled in the High-Ratio CBM + AP condition (Arm 3). Coaches may also involve parents as appropriate. Call frequency will be determined by need, primarily based on the participant’s level of adherence to the CBM program. Participants who complete at least 80% of required sessions with a accuracy rate of 80% or higher will be considered adherent to the program. Youth who are most adherent to the protocol may receive only one or two AP calls from their coach, whereas youth with inconsistent or suboptimal use of the CBM program will receive more calls, up to a total of four. Phone coaches will receive automated adherence reports by logging into the server that stores the session data (e.g., number of trials, accuracy, reaction time). Phone coaches will use these reports to determine the need for AP calls, and the type of coaching they will provide (e.g., low accuracy rate and short reaction time might suggest that youth should slow down slightly to be more accurate). Calls do not need to be once weekly, but may be concentrated (e.g., twice weekly for the first few weeks) in order to facilitate participant engagement and maximize exposure to the CBM program. Coaches will record the date, duration, and content addressed in each call.

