The phone coaches will provide the explicit rationale and instructions for the CBM intervention [29], as well as the “fear priming” instructions which encourage youth to activate anxiety fears prior to each CBM session to potentiate the effectiveness of CBM skills training [63]. The remaining content of phone coach calls will be individualized to the needs/issues of each participant, but will typically address: technical assistance (difficulty downloading CBM program, registering, creating a user account); encouragement and reinforcement for appropriate use; problem solving to overcome barriers and obstacles to use; using brief motivational enhancement techniques to encourage participants to use the program [30–32]; and/or coaching and advice to ensure high quality CBM sessions (e.g., conducting sessions at times/locations where participants will not be interrupted). If needed, phone coaches will also provide case-management and referrals for emergent clinical issues not addressed by CBM program (e.g., suicidality), although they will explicitly not themselves provide any psychosocial therapy for anxiety or any other issues.

**CBM Session review** questions will be asked of youth at 1-month follow-up. Questions ask about the number and length of sessions completed, which device was used, and interruptions during session completion.

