##### Statistical analysis

For each continuous outcome (anxiety symptoms [PARS, SCARED], depression [PHQ-9], psychopathology severity [CGI-S], psychosocial functioning [CGAS]) we will test whether there are differences between arms in the trajectories across time by fitting growth curve models in a nested two-level hierarchical linear model (HLM [64–66];).We will test the primary outcome (anxiety remission based on ADIS-C) and the CGI-I with a generalized form of HLM, using a logit link and the binomial distribution. For all HLM models, the first level of the model represents within-person variation and will include time as a predictor (3–5 timepoints, depending on the measure). The second model level represents between-person variation and includes dummy indicators for arm as the predictor variables. A significant coefficient for arm on the slope of time indicates (i.e., the cross-level interaction of arm by time) that there are different trajectories across time for each arm and will be followed with a graph to interpret the interaction(s). Assuming that the trajectories are nonlinear as is common in clinical trials (e.g., initial intervention effect upon completing the intervention and maintenance period), we will use fractional polynomials to estimate the most appropriate function for time [67, 68]. We will test our primary hypotheses using linear contrasts of the dummy vectors representing treatment arm to determine whether both High-Ratio CBM arms (2 and 3) have a different trajectory than the Low-Ratio arm, and whether High-Ratio CBM + AP (Arm 3) has a different trajectory than High-Ratio CBM Only (Arm 2). Differences at 1 month in acceptability (PAQ) and client satisfaction (CSQ-8) will be tested with a one-way ANOVA with treatment arm as the independent variable and the same a priori contrasts described above.

We will conduct the moderator analyses by adding the moderator and moderatorXarm product in the level-two HLM equation discussed above. A significant coefficient for the interaction term on the slope of time would indicate a moderator effect and will be followed up with graphs of the simple effects to determine the nature of the effect modification.

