##### Power analyses

Preliminary to calculations, we conducted a review of the adult and youth CBM anxiety literature to estimate plausible effect sizes. This included the five adult RCTs [18–22], two youth RCTs, [23, 25] and one youth case series [24]. To increase comparability across studies, we calculated within-condition effect sizes (ESs) for anxiety reduction associated with the variants of CBM most relevant for this proposal. For Low-Ratio CBM, we found a mean ES of d = 0.52. For self-administered CBM (often Internet delivered), we found a mean ES of 0.82. Lab-administered CBM yielded a mean ES of 1.39. Finally, CBM with a mix of lab and self-administered sessions yielded a mean ES similar to lab-based studies (mean d = 1.56). From this review we (a) projected the within- and between-condition ES differences we might expect in our proposed design and (b) calculated the effective ES for each of our hypotheses of clinical outcomes. For the comparison of the two High-Ratio CBM conditions vs. Low-Ratio CBM, our review suggests an estimated difference (Δ) ES of d = 0.73. We conservatively powered this analysis for an ES Δ of 0.59, approximately equivalent to an odds ratio of 2.90 [76]. To estimate the ES for the comparison of CBM + AP and High-Ratio CBM, we looked to the literature for estimates of the comparison of lab-administered vs. self-administered CBM. This review suggests an estimated ES Δ of d = 0.57. We chose to power the analysis for this hypothesis with a conservative ES Δ of d = 0.37, which is approximately equivalent to an odds ratio of 1.94 [76].

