We conducted power analyses for the primary outcome (via PASS software [77]) to generate the sample required to detect the hypothesized contrasts in a logistic regression model. For our main comparison of the two High-Ratio CBM conditions versus Low-Ratio CBM, with α = .05, we would have 80% power to detect a 20% greater remission (odds ratio = 2.90) in arms 2 + 3 compared to the Low-Ratio arm with 187 participants (n~ 63 per arm) at the 6-month follow-up**.** For the comparison of the two High-Ratio CBM conditions, at an alpha level of .05, we would have 80% power to detect a 16% greater remission (odds ratio = 1.94) in the CBM + AP arm compared to the CBM only arm with 148 participants per arm (*N* = 444 total) at the 6-month follow-up. We based our target sample on the larger N needed to adequately test this latter hypothesis (Arm 2 vs. Arm 3). To compensate for the loss in precision from imputing data for those lost to follow-up, we inflated the target sample size based on an attrition rate of ~ 10% (*N* = 498, or *n* = 166 per arm). This is a conservative adjustment, as the SEs from imputed data results will be less than the SEs from a complete case analysis.

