## Discussion

This paper describes the study protocol of a randomized controlled trial (RCT) to assess the benefit of computerized CBM to treat youth with anxiety. This RCT is considered a blended efficacy-effectiveness trial, in that it is highly controlled with detailed, blinded assessments and has a focus on possible treatment mechanisms, but is also conducted in a real-life setting with youth who have sought usual care services for anxiety and who have received a clinical anxiety diagnosis. The primary aim of this study is to assess whether self-administered CBM can be successfully delivered as a self-administered treatment at home, and whether High-Ratio CBM will demonstrate clinical effectiveness. Further, we aim to assess whether High-Ratio CBM with the AP component will result in greater rates of anxiety remission than High-Ratio CBM without AP. Finally, we aim to assess whether self-administered CBM is cost effective to deliver to youth seeking anxiety treatment in a real-world health-care setting.

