### Strengths

The study uses a rigorous control condition with a Low-Ratio CBM design, which controls for the effects of time and attention. The youth in all three arms will be asked to complete the same number of sessions over the intervention period, and in each session the youth view the same number of trials. These features bring the rigor of a classic efficacy design and permit confident attributions of outcome effects.

This study will have “effectiveness” elements (such as recruitment via electronic medical records and self-administration of CBM), which will allow us to enroll a sample that is 10 times larger than other published CBM trials. This study will be large enough to have the statistical power to pursue a wide variety of substantive, mechanistic, and economic analyses that smaller lab-based studies could not address. However, the sample will not be so large that we are unable to pursue a detailed evaluation of clinical outcomes.

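### The planned primary contrasts omit Arm 2 vs Arm 1, the only comparison that isolates High-Ratio training with coach contact equal

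*Protocol article*

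**What the plan says.** The Statistical analysis section enters dummy indicators for arm and tests the primary hypotheses with two linear contrasts. One is "to determine whether both High-Ratio CBM arms (2 and 3) have a different trajectory than the Low-Ratio arm"; the other is Arm 3 vs Arm 2. The Power analyses section opens its first calculation with "For our main comparison of the two High-Ratio CBM conditions versus Low-Ratio CBM" and sizes it on Arms 2 and 3 combined: 187 participants, about 63 per arm. It then sizes Arm 3 vs Arm 2 at 148 per arm, which sets the trial size. No Arm 2 vs Arm 1 contrast is named or powered.

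The Interventions section gives Arm 3 alone one to four coach calls of 10–30 minutes. It says that "AP procedures are intended to mimic the effects of the nonspecific, yet likely important, support and instruction provided by research staff". The calls also carry motivational techniques and instructions that "encourage youth to activate anxiety fears prior to each CBM session to potentiate the effectiveness of CBM skills training". The Design section states that participants are not blinded to AP.

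The Discussion lists among the primary aims "whether High-Ratio CBM will demonstrate clinical effectiveness", and the Abstract says the trial tests self-administered CBM both with and without AP. Under Strengths the article states: "The study uses a rigorous control condition with a Low-Ratio CBM design, which controls for the effects of time and attention". It adds that the equal number of sessions and trials, together with this control, "permit confident attributions of outcome effects".

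**The concern.** High-Ratio CBM without coaching is Arm 2, and its control is Arm 1. Those two arms differ only in the training ratio. The pooled contrast adds a group that also has coach contact, fear priming and knowledge of receiving AP. Arm 3 vs Arm 2 has no Low-Ratio control. Neither planned contrast therefore answers the question about uncoached CBM.

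A significant pooled result could come partly or wholly from AP, and the pooled test cannot say by which route. Read with the Strengths section, such a result could be taken as proof that the training works by itself at home. If Arm 2 vs Arm 1 is tested only after the data are seen, it will count as post hoc.

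**Working it through.** **Plan's own figure.** Remission rates by arm are not stated, so I solved for them from the stated differences and odds ratios (OR). A 16-point difference with OR 1.94 gives a lower rate of 34.1% or 49.9%. A 20-point difference with OR 2.90 gives 16.6% or 63.4%. For Arm 3 vs Arm 2 at 34.1% and 50.1% (mean 42.1%), two-sided .05 and 80% power:

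n = [1.96·√(2·0.421·0.579) + 0.842·√(0.341·0.659 + 0.501·0.499)]² / 0.16² = 148.3, or 149 after rounding up.

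The stated 148 per arm reproduces.

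**What the pooled contrast estimates.** Let x = Arm 2 − Arm 1 and a = Arm 3 − Arm 2. The pooled contrast is (x + (x + a))/2 = x + a/2.

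| Source in Power analyses | Pooled | a | x | AP share (a/2)/pooled |
|---|---|---|---|---|
| Powered values of d | 0.59 | 0.37 | 0.405 | 0.185/0.59 = 31% |
| Review's stated differences | 0.73 | 0.57 | 0.445 | 0.285/0.73 = 39% |
| Review's arm values 0.52, 0.82, 1.39 | (0.30 + 0.87)/2 = 0.585 | 0.57 | 0.30 | 0.285/0.585 = 49% |
| Remission, points | 20 | 16 | 20 − 16/2 = 12 | 8/20 = 40% |

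**Contact.** All arms are asked for 12 × 15 = 180 minutes of CBM. Arm 3 adds 1 × 10 = 10 to 4 × 30 = 120 coach minutes.

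**Pooled test when Arm 2 equals Arm 1.** I simulated the log-odds contrast (−1, 0.5, 0.5) with a Wald test, 148 per arm and 400,000 runs, at base rates of 16.6%, 34.1%, 49.9% and 63.4%. The nominal rate favouring High-Ratio is 2.5%.

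| Total AP effect | Pooled test favours High-Ratio | Of these, Arm 3 vs Arm 2 not significant |
|---|---|---|
| 4 points (assumed) | about 6% | 88–90% |
| 8 points (assumed) | 12–14% | 63–71% |
| 16 points (planned) | 34–46% | 11–20% |

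For the smaller AP effects, Arm 3 vs Arm 2 would usually not reveal where the pooled result came from.

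**The missing contrast.** If Arm 2 vs Arm 1 is tested only after a significant pooled contrast and the two arms are truly equal, both tests favour High-Ratio in 1.2–2.7% of trials for AP effects of 0–16 points. Its power at 148 per arm depends on the true difference:

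- d = 0.30 (0.82 − 0.52; OR = exp(0.30·π/√3) = 1.72): about 46–65% over the four base rates.
- 12 points: 70% with Arm 1 at 16.5%, falling to 55% with Arm 1 at 40%.
- d = 0.405 (OR 2.08): 74–88%.

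**The case against.** The strongest reply concerns mechanism. The article expects AP to work mainly by raising the number of CBM sessions, and fear priming is meant to strengthen the training. Home dose may simply be too low in Arm 2, an explanation the Background raises for weak home-based results. Then Arm 2 could equal Arm 1 while Arm 3 improves through training, and a positive pooled result would reflect a real High-Ratio effect at adequate dose. This stands. A reader might infer that a positive pooled result cannot reflect High-Ratio training, or that every such result with Arm 2 equal to Arm 1 is a false credit. The documents do not support either inference: they give no size for the part of AP that bypasses dose.

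Second, the two contrasts are a coherent pair that matches the stated hypotheses. With separate arm dummies, Arm 2 − Arm 1 can be recovered as the pooled contrast minus half of Arm 3 vs Arm 2. This also stands and makes the remedy cheap. The article does name its primary contrasts, however, and this one is not among them.

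Third, the Strengths section does not mention the pooled contrast. True, but the pooled contrast is the one called the main comparison, and the claim of controlled attention is not true of it.

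Fourth, the added contrast may be underpowered. The effect d = 0.405 comes from pairing 0.59 with 0.37, whereas the review's arm values give 0.30. This stands and belongs in the plan as a stated limit.

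**Conclusion.** The point holds in limited form. Both planned tests are valid for what they compare, and the randomization and sample size are not in question. What is missing is a planned test of High-Ratio training with coach contact equal, and the attribution statement is broader than the main comparison allows. By the article's own values, between 31% and 49% of the expected pooled effect is AP, depending on which effect sizes are paired.

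If uncoached High-Ratio CBM does no better than Low-Ratio, the pooled test still favours High-Ratio in up to 34–46% of trials at the planned AP effect. That figure counts the whole AP effect, including any part that runs through training dose, so it is an upper bound on misattribution. The 4- and 8-point AP effects and all base rates are assumptions, the latter solved from the article's stated differences and odds ratios.

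**What to change.** - Keep the pooled contrast and the sample size. Label the contrast 'High-Ratio CBM with or without AP vs Low-Ratio'.
- Name Arm 2 vs Arm 1 at 6 months as a planned contrast, tested at two-sided .05 only if the pooled contrast is significant. Report it with its confidence interval.
- Rest any claim for High-Ratio CBM without coaching on that contrast.
- Limit the Strengths statement on time, attention and attribution to Arm 2 vs Arm 1. The AP content need not change.

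The cost is some wording and one more contrast from the same model, with no added participants or data. The plan should state the power range above and say that a non-significant Arm 2 vs Arm 1 result is inconclusive, not evidence that uncoached CBM fails. The claim for uncoached CBM may stay unproven even when the pooled test is positive.

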## Methods

### Design

This study is approved by the Kaiser Permanente Northwest (KPNW) Internal Review Board (IRB) in Portland, Oregon. This study is a randomized controlled trial (RCT), with participants blinded to the type of CBM they receive (low vs. high ratio) but not blinded regarding receipt of AP contacts. All evaluators are blinded to participant study condition.

Participants will be randomized via computer-programming to one of three arms in a 1:1:1 ratio, stratified by age at recruitment (< age 15 vs. > = age 15) and minority status (white non-Hispanic vs. all others). Assignment will be conducted with computer-generated random block sizes of 6 or 9, masked from study staff.

Arm 1 is a Low-Ratio version of the CBM intervention, nearly indistinguishable from the other CBM version but with a lower proportion of trials that shift attention to the neutral stimuli (details below). Arm 2 is a High-Ratio CBM program, with a higher proportion of trials shifting attention to the neutral stimuli. Arm 3 is the same High-Ratio CBM program but with a component consisting of adherence promoting (AP) telephone calls from a study phone coach, from 1 to 4 total as needed. All CBM programs are self-administered on participants’ home computers.

The primary clinical outcome will be diagnostic remission at 6-month follow-up from all anxiety diagnoses present at baseline, as confirmed by the Anxiety Disorders Interview Schedule (ADIS) (see below). The secondary clinical outcomes will be the PARS, SCARED, attention bias, depression (PHQ-9), psychopathology severity (CGI-S), and psychosocial functioning (CGAS). We will also determine whether there are differences in treatment acceptability (PAQ) and satisfaction (CSQ-8). Another secondary outcome will be cost-effectiveness of the CBM intervention, as measured in incremental cost per anxiety-free-day (AFD) and cost per quality adjusted life year (QALY). Additional analyses will test whether baseline CGI-S, PHQ-9 (depression), severity of cognitive bias (ADP), gender, socio-economic status, and race/ethnicity moderate the effect of the intervention on the primary outcome. Additionally, we will test whether attention bias mediates the effect of the intervention on the 6-month remission rate and anxiety outcomes (PARS and SCARED). Lastly, we will examine whether CBM process variables (i.e., number of trials [dose], acceptable error rates, reaction time) is associated with CBM outcomes.

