### Assessments

After the preliminary screening call, interested and potentially eligible participants will complete a baseline interview where final eligibility is determined. All measures at baseline will be administered to parent and youth participants over the phone, prior to randomization. See Table 1 for the assessment schedule.

**Table 1 Tab1:** Assessment Schedule

Measures	Administration time (mins)	Respondent	Youth or Parent Sx	Timepoints*					
				S	T0	T1	T2	T3	T4
Phone eligibility screen	15	Y P	Y	x					
Youth Anxiety measures									
Anxiety Dx Interview Schedule-Child (ADIS-C)**	50	Y P	Y		x			x	x
Pediatric Anxiety Rating Scale (PARS)	15	Y P	Y		x	x	x	x	x
Screen Child Anxiety Relate Emotional Dx (SCARED)	10	Y P	Y		x	x	x	x	x
Child Avoidance Measure–Self Report (CAMS)	5	Y	Y		x	x	x	x	x
Child Avoidance Measure–Parent Report (CAMP)	5	P	P		x	x	x	x	x
Depression measures									
Patient Health Questionnaire (PHQ-9)	10	P	Y		x	x	x	x	x
Patient Health Questionnaire (PHQ-9) (Parent self-report)	5	P	P		x	x	x	x	x
Other psychopathology, improvement measures									
Clinical Global Improvement –Severity (CGI-S)	5	Y	Y		x				
Clinical Global Improvement –Improvement (CGI-I)	–	Y	Y			x	x	x	x
Psychosocial functioning, quality of life measures									
Children’s Global Adjustment Scale (CGAS)	–	Y	Y		x	x	x	x	x
Healthcare services, economic measures									
Child & Adolescent Services Assessment (CASA)	5–10	Y P	Y			x	x	x	x
EQ5D	5	Y P	Y		x	x	x	x	x
Other measures									
Demographics	5	P	–		x				
State Trait Anxiety Inventory (STAI) – State	5	P	P		x	x	x	x	x
Peterson Pubertal Development Scale (PDS)	5	Y	Y		x				
Insomnia Severity Index (ISI)	5	Y	Y		x	x	x	x	x
Participant Acceptability Questionnaire (PAQ)	5	Y P	–			x			
Client Satisfaction Questionnaire (CSQ-8)	5	Y P	Y			x			
U Rhode Island Change Assessment (URICA-S)	5	Y	Y		x	x			
Instrumental Variables (IV)	5	Y	Y		x				
CBM session review	5	Y	Y			x			
Treatment adherence and process data	–	–			x	x	x	x	x

*Timepoints: S = Screening; T0 = Baseline; T1 = 1-month follow-up; T2 = 3-month follow-up; T3 = 6-month follow-up; T4 = 12-month follow-up

** Primary outcome, ADIS anxiety and depression modules only

**health care utilization data obtained from the HMO administrative data system

Dx = diagnoses/disorders, Sx = symptoms, Y=Youth, P=Parent, I=Interviewer

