### Measures

#### Youth anxiety

The **Anxiety Disorders Interview Schedule for Children (ADIS-C)** [34, 35] is a semi-structured interview developed to identify the presence, severity, and level of interference of anxiety disorders in children aged 6–18 years old. It will be administered to youth and parents to yield Diagnostic and Statistical Manual of Mental Disorders (DSM) diagnoses of generalized anxiety disorder (GAD), social phobia (SP), and/or separation anxiety diagnoses needed to qualify for participation in the study. The trial primary outcome was also derived from this ADIS assessment: anxiety diagnosis remission at the 6-month follow-up. The ADIS will only be administered at the baseline, 6-month, and 12-month interviews. Before conducting ADIS interviews, staff must reach a criterion of 100% diagnostic correspondence with a senior staff on two consecutive interviews. All interviews will be digitally recorded; a random 10% of baseline assessments completed by each evaluation staff will be re-rated by a senior staff member.

The **Pediatric Anxiety Rating Scale (PARS)** [36] is a secondary outcome measure. This 50-item measure integrates youth and parent report of the severity of anxiety symptoms, as well as related functional impairment. Several versions of PARS scoring are available and used in the literature. To allow for comparison with other similar studies, we will calculate a total PARS score as the sum of items 2–7, with a total score ranging from 0 to 30 [37]. The PARS has high inter-rater reliability, fair internal consistency and test-retest reliability, convergent and divergent validity, and sensitivity to treatment effects [36, 38].

The **Screen for Child Anxiety Related Emotional Disorders (SCARED)** [39] is a 41-item measure of anxiety symptoms with youth- and parent-reported versions, with scores of > 25 indicating significant anxiety (total range 0 to 82). The SCARED has been validated in diverse clinical and community samples, with good internal consistency, and has detected clinical improvement in randomized clinical trials of treatment for youth anxiety [38]. We will examine the SCARED as a secondary outcome in this trial.

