We will test whether attention bias mediates between treatment and the primary outcome (remission status), by regressing Wk 2 attention bias on attention bias at baseline and study arm indicators, and by regressing remission status (using logistic regression) at one month on attention bias at 2 weeks and study arm indicators. Using the product coefficients approach to mediation [69–71], we will use the resulting regression coefficients and standard errors (SEs) to estimate the indirect effect. Because SEs of the products of regression coefficients are not normal, we will use bias-corrected bootstrapping to estimate the SEs for the indirect effect [72].

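### The mediation model takes remission at one month as its outcome, but remission is measured only at 6 and 12 months and the stated aim is 6-month remission

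*Protocol article*

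**What the plan says.** All references are to the protocol article.

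- **Mediation model (Statistical analysis).** The paragraph opens: "We will test whether attention bias mediates between treatment and the primary outcome (remission status". It then gives two regressions. In the first, week-2 attention bias is regressed on baseline attention bias and the arm indicators. The second is fitted "by regressing remission status (using logistic regression) at one month on attention bias at 2 weeks and study arm indicators". The indirect effect is the product of coefficients, with bias-corrected bootstrapping.
- **Mediation aim (Design).** "we will test whether attention bias mediates the effect of the intervention on the 6-month remission rate and anxiety outcomes (PARS and SCARED".
- **Primary outcome (Design).** "The primary clinical outcome will be diagnostic remission at 6-month follow-up from all anxiety diagnoses present at baseline", as confirmed by the ADIS.
- **Source of remission (Youth anxiety).** "The trial primary outcome was also derived from this ADIS assessment: anxiety diagnosis remission at the 6-month follow-up". The same paragraph fixes the schedule: "The ADIS will only be administered at the baseline, 6-month, and 12-month interviews".
- **Main model (Statistical analysis).** "We will test the primary outcome (anxiety remission based on ADIS-C) and the CGI-I with a generalized form of HLM", so remission is tied to the ADIS here as well.
- **Table 1 (Assessments).** The ADIS-C row is marked at T0, T3 and T4 and is blank at T1 and T2. The key reads: "T1 = 1-month follow-up; T2 = 3-month follow-up; T3 = 6-month follow-up; T4 = 12-month follow-up". There is no 2-week column and no row for attention bias.

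**The concern.** A regression needs an outcome that somebody measured. The paragraph equates remission status with the primary outcome and then dates it to a wave at which the defining interview is not given. An analyst following the text has nothing to fit and must choose a substitute: move the outcome to 6 months, or build some form of remission from the symptom scales collected at one month. These are different questions about mechanism, and the choice would be made outside the published plan.

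Two further features of the same paragraph matter once the date is corrected. The outcome equation holds only the mediator and arm, although the mediator equation adjusts for baseline bias. And the mediator is dated to week 2, when no bias assessment is scheduled. What is at stake is the mechanism analysis, which the Background lists among the efficacy features of the trial.

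**Working it through.** No sample size, power or alpha figure bears on this point, so there is no figure to reproduce. The check sets the sections side by side.

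**Step 1: is remission observed at one month?** Table 1 has five assessment waves from baseline on (T0 to T4), of which four are follow-ups. The ADIS is given at three of the five (T0, T3, T4), so at two of the four follow-ups: 6 and 12 months. One month is T1, where the ADIS-C cell is blank. The text under Youth anxiety agrees with the table. Scheduled ADIS outcomes at one month: 0 of the 498 planned participants.

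**Step 2: does another definition of remission fill the gap?**

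- The CGI-I is collected at T1, but the section on other psychopathology uses it to define response to treatment, not remission.
- The PARS and SCARED are collected at T1. The SCARED has a cut-off for significant anxiety, but no remission rule is built on it or on the PARS.
- The growth models allow 3 to 5 timepoints depending on the measure. Three ADIS waves fit that range, so it does not imply a 1-month ADIS.
- Direct maximum likelihood (Missing data) uses each participant's available data. It cannot supply a wave that is unmeasured for everyone by design.

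None of these gives a remission status at one month.

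**Step 3: does the model match the aim?** Design names the 6-month remission rate; the mediation paragraph names one month. The two conflict whatever the answer to step 2.

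**Step 4: covariates of the two equations as written.**

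| Equation | Outcome | Predictors |
|---|---|---|
| Mediator | Week-2 bias | Baseline bias, arm |
| Outcome | Remission | Week-2 bias, arm |

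Randomization balances baseline characteristics between arms. It does not balance them across levels of week-2 bias, so the mediator coefficient in the second equation is an observational association. The plan treats baseline bias as a predictor of the mediator. Population and recruitment reports literature linking higher pre-treatment bias to better outcomes, while calling that literature suggestive only. A variable plausibly related to both is therefore left out of the second equation. How far this moves the indirect effect cannot be calculated from the document.

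**Step 5: is the mediator scheduled?** The Assessments section has youth complete a single session at each follow-up to measure bias, and the first follow-up is at one month. Treatment adherence and process data says that the program records adherence data automatically, but no section says that a week-2 bias score is derived from training sessions. In the High-Ratio arms the probe always follows the neutral face in mixed pairs, whereas in the Low-Ratio arm the split is 50–50. How comparable scores would be obtained across arms from such sessions is not explained.

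**The case against.** The strongest reply is that this is one misdated clause in an additional analysis. Design introduces mediation after the primary outcome, the secondary outcomes and the moderators. Nothing in the primary contrasts, the sample size or the ADIS schedule depends on it. The intended outcome can also be recovered, since the paragraph itself points to the primary outcome, which is fixed at 6 months elsewhere. All of this stands, and it sets the grade of the point. It does not remove the contradiction: the clause still specifies a regression that cannot be run.

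A second reply is that the covariate list of a secondary model is detail that a condensed article may leave to an analysis plan. That has force for baseline severity, which the article mentions in neither equation. It has less force for baseline bias, because the article does list the predictors of both equations and puts baseline bias in only one.

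A reader might go further and infer that the indirect effect is known to be confounded by baseline bias and by baseline severity. The document does not support that. Nothing in it shows that baseline severity drives week-2 bias, and its evidence on baseline bias and outcome is hedged. A reader might also infer that repair is a matter of wording alone because every variable is already collected. That holds for ADIS remission at 6 months, the 1-month PARS and SCARED, and the baseline severity measures. It is not established for week-2 attention bias.

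**Conclusion.** Wrong as written, in a secondary analysis; it should be fixed. The outcome equation has no data at the stated wave and contradicts the stated aim. This conclusion needs no assumption beyond reading remission status as ADIS-based, which the mediation paragraph does by equating it with the primary outcome. The count of 0 of 498 restates the schedule; it does not measure harm to any trial conclusion.

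The omission of baseline bias from the outcome equation is a subordinate point: adding it is sound practice, with a benefit of unknown size. The week-2 mediator is a gap to reconcile, since the document neither schedules the measurement nor says where it would come from. A reader might take the point to threaten the trial's main result. It does not, because the primary arm comparisons rest on ADIS waves that are scheduled.

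**What to change.** In the mediation paragraph of Statistical analysis:

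1. **Outcome.** Replace one-month remission with ADIS remission at 6 months, in line with Design. If an earlier outcome is wanted, use the 1-month PARS and SCARED, which are collected at T1 and named in the mediation aim.
2. **Covariates.** Put baseline attention bias in the outcome equation as well as the mediator equation. Baseline severity (PARS or CGI-S, both collected at T0) is a reasonable further covariate.
3. **Mediator.** Either state where the week-2 bias score comes from and how it is computed in each arm, or use the 1-month bias measurement, which precedes the 6-month outcome. The choices are linked: with the 1-month measurement, mediator and outcome would be concurrent if the 1-month PARS or SCARED were the outcome, so that pairing should be avoided.

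Cost: items 1 and 2 change analysis wording only, because the outcomes and severity measures are already scheduled and baseline bias is already required by the mediator equation. Item 3 is also only wording if the 1-month measurement is adopted. If week 2 is kept, the sponsor must first confirm that a usable score exists.
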